### Randomisation

Randomisation was stratified by primary care trust. In Sandwell PCT, after discussion with the case finding programme manager, it was agreed that 11 practices were a higher priority for the case finding intervention and the remaining 15 practices were a lower priority. It was therefore decided to stratify the practices into two groups for randomisation: early intervention and late intervention. A table of random numbers was generated to determine the order in which practices should receive the project nurse led intervention in the early intervention group and a second table for practices in the late intervention group.

The six practices in Solihull were of different characteristics, two were single handed and two were located very near each other and served similar populations. They were therefore stratified into three pairs (two single handed, two similar location and two remaining practices) for randomisation. A table of random numbers was generated to determine which of each pair should have the intervention first and which second.

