The primary aim of the study is to evaluate whether there is a difference in proportion of eligible patients on the relevant prescription medication before and after the practice was exposed to the intervention. In statistical terms this null-hypothesis (no difference) can be tested using a mixed logistic regression model with binary outcome (prescription of the appropriate medication). Important independent variables to consider are the clustering effect (i.e. effect of GP practice), calendar time effect (since the intervention is sequentially rolled-out) and an indicator of intervention exposure for each practice at each time point; in an to adjustment for other characteristics [4]. These models will be fitted using population averaged models using GEE methods in STATA, allowing for clustering and adjusting for individual level covariates and any cluster level covariates where available. Population averaged models as opposed to random effects models (also known as marginal models) will be used as within the framework of cluster randomised trials, random effects models both lack appropriate interpretation and might be biased
[31]. The covariates to be included in the adjustment will be pre-specified and will include practice size and patient level characteristics (age, sex, diabetic status, smoking status, blood pressure, total cholesterol and HDL cholesterol); GP practice will be included as a random effect; time point as a fixed effect; and exposure or non-exposure as the main intervention effect. Null hypotheses for secondary outcomes take a similar form to that for the primary outcome. Analysis of the secondary outcomes will take a similar form to that described for the primary outcome.

The primary outcome will be considered significant at the 5% level and so 95% confidence intervals (CIs) reported; whereas secondary outcomes will be deemed significant at the 1% level (and so 99% CIs reported). This difference in levels of significance, give more weight to the primary outcomes. Analysis will be stratified by primary care trust: the analysis of the project nurse led intervention in Sandwell and the prescribing advisor led intervention in Solihull will be carried out separately.

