### Sample size & number of practices

Since the analysis is to be stratified by primary care trust sample size calculations were also stratified by trust. However, since this is a pragmatic evaluation the study has a limited sample size to those practices which agreed to participate in the evaluation. In the Solihull trust only 6 practices agreed to participate and it was not expected that this would provide adequate power. We therefore based power calculations on the Sandwell part of the study only. In the pilot study approximately 5% to 6% of registered patients in each practice were found to be untreated high risk patients. In Sandwell this means we expect to invite between 6,241 and 7,489 untreated high-risk patients from a total registered population of 124,820. From this fixed study size, it is possible to estimate the difference that will be detectable (difference between patients exposed and not exposed to the intervention in proportion of eligible patients medicated). These patients are spread across 26 clusters, each with a conservative estimate of average size of 240 (assuming 5% of patients eligible); but with some variation between practices sizes with coefficient of variation of 0.74.

The difference detectable depends on the level of intra-cluster correlation (ICC), the variation in sizes of practices, and the proportion of patients medicated in the control arm. Estimates of ICC would ideally come from other similar studies, but in the absence of such evidence we are guided by a review of estimates of ICCs which found that ICC values are typically between 0.02 and 0.1
[32]. The stepped wedge nature of this study should mean that impact of intra-cluster correlations are lower than in conventional cluster trials
[4], so these values can be viewed as conservative. The pilot study estimated that the proportion of eligible patients started on medication over the course of one year is around 13%.

So, using several different estimates of likely values of ICCs and current proportions of patients medicated, we have estimated what values for outcomes post intervention could be detected (all for 80% power, 5% significance and coefficient of variation of 0.74). We have used conventional cluster RCT power calculation methods since this study is a modification of the conventional stepped wedge design and so provide conservative estimates
[33].

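### Solihull is given the same 5% GEE significance rule as Sandwell although it has six practices randomised in three pairs, and the plan does not say which trust's test answers the primary hypothesis

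*Protocol article*

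**What the plan says.** The Background states one primary hypothesis: targeted case finding raises the rate at which high-risk patients start treatment.

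The Analysis section gives one method for both trusts: "These models will be fitted using population averaged models using GEE methods in STATA, allowing for clustering", with "time point as a fixed effect". The decision rule is "The primary outcome will be considered significant at the 5% level and so 95% confidence intervals (CIs) reported", with 1% and 99% intervals for secondary outcomes. The section closes by saying that "the analysis of the project nurse led intervention in Sandwell and the prescribing advisor led intervention in Solihull will be carried out separately". Nothing exempts Solihull from the model or the significance levels.

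On the Solihull practices, the Randomisation section says "They were therefore stratified into three pairs", and then "A table of random numbers was generated to determine which of each pair should have the intervention first and which second". It does not describe the order of the pairs as random.

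The sample size section says "In the Solihull trust only 6 practices agreed to participate and it was not expected that this would provide adequate power", and bases its power calculation on Sandwell only. The Discussion lists the small number of clusters as a limitation, cites guidance of at least 10 clusters per arm, and suggests that the stepped wedge may mitigate the problem.

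**The concern.** Three stated choices do not fit together: a separate Solihull analysis, a 5% rule without exception, and a Solihull randomisation with very few possible outcomes.

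The article admits low power in Solihull, but low power warns only of a missed effect. The opposite error is not addressed. The usual GEE standard errors and normal reference rely on many clusters. With six, the standard error can be too small and a null effect can look significant too often. The Discussion's mitigating argument, that intra-cluster correlation matters less when each practice is its own control, concerns precision. It does not make a standard error estimated from six practices reliable.

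The plan also has one primary hypothesis and two 5% tests of it, without saying which one decides. At stake is how a significant Solihull result, or a disagreement between the trusts, would be read.

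**Working it through.** **Inputs from the protocol article.** Six Solihull practices in three pairs; 18,938 registered patients, 945 of them expected to be untreated and at high risk; 13% started on treatment without the intervention; intra-cluster correlation (ICC) 0.01, 0.05 and 0.1, as in the article's worked examples; coefficient of variation (CV) of practice size 0.74, which the article gives for Sandwell.

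**The article's own Solihull figure.** 0.05 × 18,938 = 946.9, against 945 stated, so it reproduces within rounding. Mean size is 945 / 6 = 157.5 per practice. The article states no power or type I error for Solihull.

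**Randomisation count.** Two orders in each of three pairs gives 2^3 = 8 allocations. The smallest one-sided p-value is 1/8 = 0.125. For a symmetric two-sided statistic it is 2/8 = 0.25. Both exceed 0.05 and 0.01. If the order of the pairs had also been random, there would be 3! × 8 = 48 sequences and a two-sided minimum of 2/48 = 0.042, which passes 5% but not 1%.

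**Analytic size, three practices against three.** The uncorrected sandwich divides by 3 rather than 2 within each group, so its variance is 2/3 of the unbiased one. A nominal 5% z-test then rejects when |t| on 4 df exceeds 1.96 × √(2/3) = 1.600. That probability is 18.5%. With the variance multiplied by 6/5, the threshold is 1.96 × √(2/3 × 6/5) = 1.753 and the probability 15.4%.

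**Simulated size under no effect.** Logistic GEE, exchangeable working correlation, fixed time effects, about 1,000 runs per scenario. Each cell shows the range over ICC 0.01, 0.05 and 0.1. The ratio is the between-period to within-period correlation.

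| Design | Sizes | Sandwich, z | Sandwich × 6/5, t on 4 df | Model-based SE, z |
|---|---|---|---|---|
| 3 v 3 parallel | equal | 16.3–18.6% | 4.9–5.5% | 13.6–16.5% |
| 3 v 3 parallel | CV 0.74 | 20.2–27.9% | 7.5–14.2% | 19.6–20.7% |
| Two-step, ratio 1.0 | equal | 19.7–21.9% | 7.0–8.7% | 4.0–7.1% |
| Two-step, ratio 1.0 | CV 0.74 | 24.1–27.3% | 10.3–10.8% | 5.5–10.0% |
| Two-step, ratio 0.8 | equal | 18.3–20.6% | 6.6–7.7% | 9.4–31.3% |
| Two-step, ratio 0.8 | CV 0.74 | 24.3–28.5% | 10.2–12.4% | 12.1–33.7% |
| Six-step, ratio 1.0 | equal | 18.8–19.4% | 6.1–7.0% | 4.5–6.5% |
| Six-step, ratio 1.0 | CV 0.74 | 20.0–21.9% | 7.9–9.2% | 4.7–9.1% |
| Six-step, ratio 0.8* | equal | 16.7–18.0% | 5.5–6.2% | 10.6–21.5% |
| Six-step, ratio 0.8* | CV 0.74 | 22.3–23.8% | 7.9–10.1% | 13.7–23.8% |

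*ICC 0.01 and 0.05 only; the ICC 0.1 runs did not finish.

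Monte Carlo error is about √(0.19 × 0.81 / 1000) = 1.2 percentage points at a rate of 19%. The uncorrected sandwich z-test is too liberal in every row. A model-based standard error is near nominal in the stepped designs only when the working correlation is right and practices are of similar size. The simple correction with a t reference helps most, but still reaches 14% when sizes vary.

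**Assumptions not in the article.** CV 0.74 applied to Solihull, the number of steps, and the correlation ratios 1.0 and 0.8. The simulations carried time and exposure only; the planned adjustment for practice size and patient characteristics was not simulated.

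**The case against.** The eight-allocation limit binds only tests based on the randomisation. A reader might infer that no valid Solihull test can reach 5%. The documents do not support that: the plan is a regression, and a small-sample t-test (on 4 df, or paired on 2 df with critical value 4.30) can reach 5% and is valid if its model assumptions hold.

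A reader might also infer that the planned test has a false-positive rate of 19%. That figure belongs to an uncorrected sandwich with a normal reference, which the article never names. It says GEE in Stata, and elsewhere speaks of a mixed model with practice as a random effect. The variance estimator and any correction may be set out in an analysis plan that is not shown, and their absence from an article is not a fault. This objection stands, so the error rates are conditional.

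The trusts also receive different interventions, nurse-led and prescribing-advisor-led, so separate analyses are reasonable. No text says that significance in either trust would count as success. Two valid, independent 5% tests would give 1 − 0.95² = 9.75% for at least one false positive, but that matters only under such a rule. The Abstract describes only the 26 Sandwell practices, and power rests on Sandwell, which hints that Sandwell is the main analysis. A hint is not a decision rule, however, and the Analysis section applies 5% to both.

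The Intervention section speaks of a sequence determined by the randomisation, so random pair order cannot be excluded. Eight is nevertheless the natural reading of the Randomisation section.

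**Conclusion.** The concern holds in limited form. The article fixes a separate 5% test (1% for secondary outcomes) for six practices whose described randomisation cannot by itself support significance at either level. A significant Solihull result would therefore depend on model assumptions that six clusters can hardly check.

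The size of the problem depends on an unnamed variance estimator: about 16% to 29% with an uncorrected sandwich and z reference, about 5% to 14% with the 6/5 factor and t on 4 df, and about 4% to 34% with a model-based standard error. These figures rest on the assumed practice-size variation, steps and correlation decay listed above. The count of eight rests on the pair order being fixed.

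Separately, the plan leaves open which of the two tests answers its single primary hypothesis. The admissions of low power and few clusters cover neither point.

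**What to change.** State in the Analysis section that Sandwell is the single confirmatory analysis of the primary outcome at 5%. State that Solihull will be reported as an effect estimate with a small-sample-corrected interval, for example a bias-corrected variance with a t reference, and that no significance claim will be made there for primary or secondary outcomes. Name the variance estimator and reference distribution for Solihull. Since the simple correction still reached 14% in one scenario, it reduces the problem without fully removing it, so it should accompany the descriptive label rather than replace it.

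The change is one of wording: no data, practice or analysis is lost. The cost is giving up a Solihull significance claim that the design does not support.

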### Sample size & number of practices

Since the analysis is to be stratified by primary care trust sample size calculations were also stratified by trust. However, since this is a pragmatic evaluation the study has a limited sample size to those practices which agreed to participate in the evaluation. In the Solihull trust only 6 practices agreed to participate and it was not expected that this would provide adequate power. We therefore based power calculations on the Sandwell part of the study only. In the pilot study approximately 5% to 6% of registered patients in each practice were found to be untreated high risk patients. In Sandwell this means we expect to invite between 6,241 and 7,489 untreated high-risk patients from a total registered population of 124,820. From this fixed study size, it is possible to estimate the difference that will be detectable (difference between patients exposed and not exposed to the intervention in proportion of eligible patients medicated). These patients are spread across 26 clusters, each with a conservative estimate of average size of 240 (assuming 5% of patients eligible); but with some variation between practices sizes with coefficient of variation of 0.74.

The difference detectable depends on the level of intra-cluster correlation (ICC), the variation in sizes of practices, and the proportion of patients medicated in the control arm. Estimates of ICC would ideally come from other similar studies, but in the absence of such evidence we are guided by a review of estimates of ICCs which found that ICC values are typically between 0.02 and 0.1
[32]. The stepped wedge nature of this study should mean that impact of intra-cluster correlations are lower than in conventional cluster trials
[4], so these values can be viewed as conservative. The pilot study estimated that the proportion of eligible patients started on medication over the course of one year is around 13%.

So, using several different estimates of likely values of ICCs and current proportions of patients medicated, we have estimated what values for outcomes post intervention could be detected (all for 80% power, 5% significance and coefficient of variation of 0.74). We have used conventional cluster RCT power calculation methods since this study is a modification of the conventional stepped wedge design and so provide conservative estimates
[33].

For example, if the current proportion of patients medicated is about 13%, and values for intra cluster correlation low (ICC of 0.01) then this study would be powered to detect an increase in proportion of high risk patients started on treatment to 19% (a relative risk of 1.46); with an ICC of 0.05 the study would detect an increase to 21% (relative risk 1.62); with an ICC of 0.1 the study would detect an increase to 26% (relative risk 2.00). If however the current proportion of patients medicated was closer to 20% and the ICC much higher (say 0.1) then this study would provide 80% power to detect an increase to 40% (that is almost a 20% absolute percentage increase).

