[35]. In this setting we are limited by the number of GP practices in the two primary care trusts. However, the stepped wedge nature of this design, in which all practices will eventually receive the intervention, but the order in which they do so will be randomised, does provide a more robust design over the conventional cluster randomized trial and so may mitigate some of the potential issues surrounding the inclusion of what might be considered as a small number of clusters. This is because within a stepped wedge design each clusters acts as its own control (during the period in which the cluster is not receiving the intervention) and it has been shown that magnitudes of intra-cluster correlations are less important
[36]. Furthermore, this study is a modification of the common step-wedge design because after completion of case finding the intervention is not maintained in the clusters (rather the nurse who delivers the intervention moves to the next practice). In effect, this probably means a reduced level of power to detect an effect of the intervention due to contamination of patients not exposed but nonetheless contributing to the analysis in later wedges.

Routine data on prescription of antihypertensives and statins is a pragmatic and easily collected outcome. However this leaves the study vulnerable to primary non compliance as not all those who are issued prescriptions take them.

We hope to be able to determine whether case finding is more effective and cost effective in achieving higher rates of uptake of preventative advice and treatment; whether it results in a reduction in outpatient referrals and admissions to hospital for CVD related events; and whether it is acceptable to clinicians and patients.

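### The detectable proportions from 13% at ICC 0.05 (21%) and ICC 0.10 (26%) do not follow from the stated power method, and the two ICC 0.10 examples contradict each other

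*Protocol article*

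**What the plan says.** The protocol's section on sample size and number of practices treats the study size as fixed and works out what difference it could detect in Sandwell. It sets the inputs once for every scenario. On clusters: "These patients are spread across 26 clusters, each with a conservative estimate of average size of 240". On error rates and size variation: "all for 80% power, 5% significance and coefficient of variation of 0.74". The method is named as the conventional one for cluster randomised trials, and is described as conservative for this design. The ICC is guided by a review in which "ICC values are typically between 0.02 and 0.1".

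Four results follow:

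- from 13%, ICC 0.01: detectable 19%, relative risk 1.46;
- from 13%, ICC 0.05: "with an ICC of 0.05 the study would detect an increase to 21% (relative risk 1.62");
- from 13%, ICC 0.10: "with an ICC of 0.1 the study would detect an increase to 26% (relative risk 2.00");
- from 20%, ICC 0.10: "then this study would provide 80% power to detect an increase to 40" per cent.

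The section does not state how the 26 practices are split for the calculation, whether the test is one- or two-sided, or which design-effect formula was used.

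**The concern.** The third and fourth results share the same ICC, clusters, CV, power and significance level, and differ only in the control proportion. Yet one detects a rise of 13 percentage points and the other needs 20. Moving the control proportion from 13% to 20% raises the binomial variance, but not by enough to explain that gap. The first two results look odd as well: a fivefold rise in the ICC, with clusters of 240, moves the detectable proportion only from 19% to 21%.

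These are the only numerical power statements in the document, and the abstract's claim of sufficient power has no other numerical support. Both doubtful figures lie inside the ICC range that the section calls typical. Someone interpreting a null result, or planning a similar trial from this article, would take a relative risk of 1.62 at ICC 0.05 as detectable with 80% power by conventional methods.

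**Working it through.** **Inputs.** From the sample size section: 26 practices, mean size m = 240, CV = 0.74, 80% power, 5% significance, control proportion 13% or 20%. Assumed, because not stated: 13 practices per arm, a two-sided test, and the usual design effect for unequal cluster sizes.

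**Formulas.**

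- Design effect: DE = 1 + [(1 + CV²)m − 1] × ICC. Here (1 + 0.74²) × 240 = 371.4, so DE = 1 + 370.4 × ICC.
- Effective patients per arm: n = 13 × 240 / DE = 3,120 / DE.
- Required n per arm for p1 v p2: n = [1.96√(2p̄(1−p̄)) + 0.842√(p1(1−p1) + p2(1−p2))]² / (p2−p1)², where p̄ is the mean of p1 and p2. The detectable p2 solves this for the available n.

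**Step 1: a check that needs no design effect.** At one ICC, with the same clusters and CV, both ICC 0.10 examples have the same effective sample size, whatever it is. For equal arms the formula gives:

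- 13% v 26%: about 145 per arm;
- 20% v 40%: about 81 per arm.

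They cannot both be right. If 40% is right, the detectable proportion from 13% is about 31%. If 26% is right, the detectable proportion from 20% is about 35%. Rounding does not close the gap: 13% v 26.5% still needs about 135.

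**Step 2: all four figures under the assumed conventions.**

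| Control | ICC | DE | n per arm | Stated | Recomputed | Power at stated figure |
|---|---|---|---|---|---|---|
| 13% | 0.01 | 4.70 | 663 | 19% | 18.6% | 85% |
| 20% | 0.10 | 38.04 | 82 | 40% | 39.9% | 80.4% |
| 13% | 0.05 | 19.52 | 160 | 21% | 25.3% | 47.8% |
| 13% | 0.10 | 38.04 | 82 | 26% | 31.0% | 55.7% |

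The first two rows reproduce the protocol to the nearest whole per cent, which supports the assumed split and formula. The last two do not. The recomputed relative risks are 25.3/13 = 1.94 (stated 1.62) and 31.0/13 = 2.38 (stated 2.00). The detectable proportion is understated by about 4 points at ICC 0.05 and 5 points at ICC 0.10.

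**Step 3: other conventions.** Power at 13% v 21% (ICC 0.05) and at 13% v 26% (ICC 0.10):

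- cluster-size variation ignored (with m = 288): 65% and 74%;
- minimum-variance weighting of unequal clusters: 63% and 73%;
- t distribution instead of normal: 45% and 53%;
- mean size 288 (7,489 / 26, the upper end of the patient range): 48% and 56%.

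A one-sided 5% test detects 23.7% and 28.7%, still above 21% and 26%. Counting 26 practices in each arm gives 21.3% and 25.1%, close to the two disputed figures. But that doubles the sample, and the other two results would then be 16.9% and 33.7% instead of 19% and 40%. None of the conventions tried reproduces all four figures.

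**The case against.** The strongest reply is that 48% and 56% are powers of a parallel-group stand-in, not of this trial. That stands. As an illustration, a standard stepped wedge calculation with 26 practices, 240 patients per practice spread over the periods and 2 to 26 steps gives 98% power or more at both disputed effects. It still gives about 92% or more when m is divided by 1 + CV². That calculation is optimistic, since it assumes an immediate, maintained effect and one ICC across periods. It nevertheless shows why a reader who infers from the wrong figures that the trial is underpowered would go further than the document allows. The reply does not rescue the figures, which are presented as output of the conventional method and must follow from it.

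The sample was also not chosen from these figures. It was limited to the practices available, and the rollout was going ahead regardless. Under the conventional method the pilot contrast of 41% v 13% has about 99% power at ICC 0.10. Both points stand, and they confine the matter to the reported numbers.

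Four further inferences are tempting but not supported:

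- *The whole typical ICC range is understated.* The shortfall is shown at two ICC values from 13%. Nothing is stated at ICC 0.02, and the 20% to 40% example at ICC 0.10 reproduces.
- *The claim of conservatism contradicts the Discussion.* The Discussion says of the non-maintained intervention that "this probably means a reduced level of power to detect an effect of the intervention". This can be read as a loss against a standard stepped wedge, and such a design could still exceed a parallel trial.
- *The ICC 0.01 example is misleading.* It lies below the quoted range, but the text already labels it as low.
- *The ICC labels slipped by one.* The stated 21% and 26% are close to the results at ICC 0.02 (20.7%) and 0.05 (25.3%), but the document does not say how the figures arose.

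**Conclusion.** The point holds for two figures. The detectable proportions of 21% (ICC 0.05) and 26% (ICC 0.10) from 13% are wrong as results of the stated method. The contradiction between the two ICC 0.10 examples rests only on their shared inputs. The corrected values of about 25% and 31%, and the powers of about 48% and 56%, rest on three unstated assumptions: 13 practices per arm, a two-sided test and the usual CV-inflated design effect. The match with the stated 19% and 40% supports these assumptions but does not prove them. The conclusion is about the quoted figures. The actual power of the stepped wedge design is not determined by this check.

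**What to change.** Recompute the two figures and restate them with their relative risks. Under the assumptions above they become about 25% (relative risk 1.9) at ICC 0.05 and about 31% (relative risk 2.4) at ICC 0.10. State the split of practices, the sidedness of the test and the design-effect formula, so that all four results can be reproduced from one set of inputs. If the authors used another convention, they should name it and bring all four figures into line with it.

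The cost is one reworded paragraph. Under these assumptions the restated figures are less favourable; sample size, randomisation, data collection and analysis stay as they are.
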